### Data analysis

#### Sample size assumptions

For Aim 1, our estimated sample size of 750 individuals using RDS was calculated based on feasibility. Previous work suggests PWUD compared to non-users have a 2–6 fold increase in TB prevalence, translating into potentially detecting 30–90 TB cases from Aim 1 [12]. TB prevalence among the general population is estimated to range between 1–4% [32]. We assumed prevalence of drug use at 2.6% in the general population [54] and an estimated design effect (DE) of 4 allowing us to detect a three-fold increase in prevalence to 7.2% for PWUD with 80% power; if DE = 2 we can detect a two-fold increase to 5.7%. We therefore concluded that this sample size was appropriate under a variety of reasonable assumptions. Our sample size continues to provide 80% power if prevalence increases to 3%. The incipient disease signature prevalence in the community has been estimated at 13%, meaning that we have 80% power to detect a 1.4 (DE = 2) or 1.5 (DE = 4) fold increase in incipient disease among PWUD.

For Aim 2, other studies have consistently estimated that individuals who are in close contact with one another are linked by WGS in more than 70% of the sample [55]. If this is the case among PWUD, then for a sample size of 50 individuals, our precision will be 24.6% meaning our 95% confidence interval (CI) will range from 56.2% to 80.9%.

Patterson et al. found that 43% of individuals who had tested positive for drug-sensitive pulmonary TB by with Xpert Ultra had positive cough aerosols and those with non-zero colony forming units (CFU) measuring bacterial load had a median of 2.5 CFU [38]. Assuming that this is similar in controls, this would mean that by enrolling of 50 PWUD and 50 controls for Aim 3, we have 80% power to detect a 70% positive CFU probability in PWUD. Among those positive, we have 80% power to detect a 2.5-fold increase in the median CFU value with Mann-Whitney test and assuming CFU values are exponentially distributed. Similarly, assuming exhalation pattern frequency of 23.9 in controls, we have 80% power to detect a 2-fold increase in median exhalation frequency between PWUD and controls to enable us to demonstrate good power for the hypothesized drug use effect.

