## Methods

TOTAL is a cross-sectional, observational study. The protocol for this study was developed using the Strengthening the Reporting of Observational Studies in Epidemiology (STROBE) guidelines [33] and this checklist can be found in S1 Checklist. For Aim 1, RDS will be used to recruit 750 people who use methamphetamine and/or Mandrax. For Aim 2, we will screen and enroll those participants from Aim 1 with TB disease based on positive microbiology (projected 45–75 participants) to estimate the proportion that reflect recent TB transmission via Whole Genome Sequencing (WGS) and social epidemiologic links. For Aim 3, we will enroll 100 participants who are diagnosed with TB and compare PWUD (Arm 1) with people who do not use drugs (Arm 2). For Arm 1 we will recruit 50 participants, most from Aim 2, who have active, untreated pulmonary TB and use methamphetamine and/or Mandrax. For Arm 2 we will recruit 50 persons who do not smoke illicit drugs but have been newly diagnosed with TB disease and have received less than five days of treatment. The study design is shown in Fig 1.

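### The Aim 2 precision assumes 50 independent TB cases, although they come from the respondent-driven sample given a design effect of 4 or 2 for Aim 1; the stated interval is probably materially too narrow.

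*Protocol article*

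**What the plan says.** Under Sample size assumptions, the protocol article takes from other studies that "individuals who are in close contact with one another are linked by WGS in more than 70% of the sample". It applies 70% to Aim 2 and states that "for a sample size of 50 individuals, our precision will be 24.6% meaning our 95% confidence interval (CI) will range from 56.2% to 80.9" (per cent). It mentions no design effect there and gives no reason for leaving one out.

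The paragraph just before treats Aim 1 differently. For TB prevalence it uses "an estimated design effect (DE) of 4 allowing us to detect a three-fold increase in prevalence to 7.2% for PWUD with 80% power", and adds that "if DE = 2 we can detect a two-fold increase to 5.7" (per cent). For incipient disease it claims "80% power to detect a 1.4 (DE = 2) or 1.5 (DE = 4) fold increase in incipient disease among PWUD".

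The opening of Methods makes the Aim 2 participants the Aim 1 participants with microbiologically positive TB ("projected 45–75 participants"). Recruitment and assessment of primary objectives says the same, and describes coupons handed to people with whom the recruiter currently uses drugs. Assessment of primary objectives sets the Aim 2 quantity as the prevalence of cases clustered by whole genome sequencing (WGS) in the study's population of people who use drugs.

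**The concern.** There are two separate reasons to doubt that 50 Aim 2 cases carry the information of 50 independent observations.

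- **Sampling.** The cases are a subset of the same coupon chains. The article itself reckons that this recruitment multiplies variance by 2 to 4 for the Aim 1 outcomes. Dropping the inflation one paragraph later, without comment, is inconsistent.
- **Outcome.** Clustering is a property of pairs. If case A is clustered because its isolate is close to that of case B, then B is clustered as well. Recruiter and recruit use drugs together, so linked cases may also sit next to each other in a chain. The hypothesis under Primary objectives, a high proportion of linked isolates, presupposes this kind of dependence.

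At stake is what the study can say about the proportion of TB cases due to recent transmission within the network. A reader planning around a 25-point interval may get one that is a good deal wider.

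**Working it through.** **Inputs**

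- Linked proportion p = 0.70 and n = 50: Sample size assumptions, Aim 2.
- DE = 4 (main) and 2 (alternative): Sample size assumptions, Aim 1.
- 45 to 75 projected Aim 2 participants: Methods, opening paragraph.
- z = 1.96, so z² = 3.8415.

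**Formula.** The Wilson 95% interval has centre (p + z²/2n) / (1 + z²/n) and half-width z·√(p(1−p)/n + z²/4n²) / (1 + z²/n).

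**Step 1: reproduce the stated figure (n = 50, DE = 1)**

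- Centre: (0.70 + 0.0384) / 1.0768 = 0.6857.
- Half-width: 1.96 × √(0.00420 + 0.00038) / 1.0768 = 0.1232.
- Interval: 56.2% to 80.9%; full width 24.6 points.

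Both limits and the width match. Other standard methods for 35/50 do not match all three figures:

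| Method | Interval (%) | Width (points) |
|---|---|---|
| Wald | 57.3–82.7 | 25.4 |
| Clopper-Pearson | 55.4–82.1 | 26.7 |
| Agresti-Coull | 56.2–81.0 | 24.8 |
| Jeffreys | 56.4–81.3 | 24.9 |
| Wilson with continuity correction | 55.2–81.7 | 26.5 |

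The published figure is thus plain Wilson at the full n of 50. The 24.6 called precision is the full width; the half-width is about 12.3 points.

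**Step 2: carry over the Aim 1 design effects.** Replace n by the effective size n/DE.

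- DE = 2, effective n = 25: centre (0.70 + 0.0768) / 1.1537 = 0.6734; half-width 1.96 × √(0.0084 + 0.0015) / 1.1537 = 0.1694.
- DE = 4, effective n = 12.5: centre (0.70 + 0.1537) / 1.3073 = 0.6530; half-width 1.96 × √(0.0168 + 0.0061) / 1.3073 = 0.2271.

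The same calculation at both ends of the projected Aim 2 enrolment:

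| Cases | DE = 1 | DE = 2 | DE = 4 |
|---|---|---|---|
| 45 | 55.5–81.4 | 49.3–84.8 | 41.2–88.6 |
| 50 | 56.2–80.9 | 50.4–84.3 (33.9 points) | 42.6–88.0 (45.4 points) |
| 75 | 58.9–79.2 | 54.0–82.2 | 47.4–85.8 |

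**Step 3: size of the difference at n = 50.** 33.9/24.6 is about 1.4 and 45.4/24.6 is about 1.8. Keeping the stated width would take 50 × 2 = 100 cases at DE = 2 or 50 × 4 = 200 at DE = 4, against 45 to 75 projected.

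**The case against.** **The design effect is borrowed.** The article gives 2 and 4 for TB prevalence and incipient disease among all 750 participants. A design effect belongs to an outcome and a sample, and about 50 cases (50/750 = 6.7%) scattered through the chains could show less chain-related correlation. This stands: 34 to 45 points is a sensitivity range, not a derived fact, and the true inflation could be smaller or larger. It does not rescue DE = 1, which is also an assumption and is the one the article leaves unexplained.

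**The aim may be descriptive.** Primary objectives speaks of linked isolates within this cohort, and a design effect matters less for describing the observed cases. But Assessment of primary objectives names a population prevalence, and quoting a 95% confidence interval is itself a claim beyond the observed cases.

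**More cases, or a higher proportion, would help.** This is true. With 75 cases and DE = 2 the width is 28.2 points. With 90 cases, the top of the detection range under Sample size assumptions, DE = 2 leaves an effective 45 and a width of 25.9 points. A proportion above 70% also narrows the interval. None of this is the scenario printed, which is 50 cases at 70%.

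**Stronger readings that the article does not support**

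- A reader might infer that the study could no longer show that recent transmission predominates, because the interval could include 50%. No 50% threshold or test is stated, and at n = 50 with DE = 2 the lower limit is still 50.4%. It reaches 50% at an effective n of 3.8415 × 0.25 / 0.20² = 24.0, that is DE = 50/24.0, about 2.1.
- A reader might infer that the reported interval will be computed as if cases were independent. The article does not state the analysis method, which may sit in the full protocol or analysis plan.
- A reader might see a conflict between "projected 45–75 participants" and "translating into potentially detecting 30–90 TB cases from Aim 1". These are different quantities, enrolment in Aim 2 and potential detections, and the first range lies inside the second.
- A reader might infer that all 50 enrolled cases are presumed to yield a sequence. A sample size of 50 can equally mean 50 analysed.

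**Conclusion.** The point holds as an unexplained inconsistency of assumption. The arithmetic is correct for a simple random sample. The Aim 2 precision uses DE = 1 for a subset of a sample that the article otherwise credits with DE = 4 or 2, and for an outcome that is dependent between cases. The stated interval is therefore probably materially too narrow: about 1.4 times as wide at DE = 2 and 1.8 times at DE = 4, for 50 cases at 70%. These sizes rest on carrying the Aim 1 design effects over to the clustered proportion and on using n/DE in the Wilson formula. That some inflation is to be expected rests only on the recruitment design and the nature of the outcome.

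**What to change.** In Sample size assumptions, restate the Aim 2 precision under the same design effects as Aim 1: a full width of about 34 points at DE = 2 and 45 points at DE = 4 for 50 sequenced cases. Say that this range is carried over from Aim 1. Alternatively, keep DE = 1 and justify it. In either case, label 24.6 points as the full width of the interval under independence. The reported Aim 2 interval should likewise allow for dependence between cases; the choice of method can be left to the analysis plan.

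The cost is a few sentences and a less favourable stated precision. No extra participants are needed and the design does not change.

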### Exhaled bioaerosol collection

For Aim 3, exhaled bioaerosols will be collected with a modified Coriolis®μ Air Sampler, developed to quantitate the infectiousness of expired air [36]. This Respiratory Air Sampling Chamber (RASC) is used to collect and concentrate biological airborne particles (0.5–20 μm) using a high-flow wet walled cyclone, as previously described [37], with some modifications which include reducing the sampling period to two consecutive 15-minute sessions and the removal of continuous CO_2_, aerodynamic particle, temperature, and humidity monitoring. Droplet digital polymerase chain reaction (ddPCR) analysis will be used to detect *Mtb* within the exhaled air [38].

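### Aim 3 power is stated for CFU and exhalation frequency and is not shown to apply to the ddPCR outcome that the article describes and analyses

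*Protocol article*

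**What the plan says.** The Protocol article, Sample size assumptions, takes its Aim 3 inputs from a cited study of exhaled aerosol. The positivity input is "43% of individuals who had tested positive for drug-sensitive pulmonary TB by with Xpert Ultra had positive cough aerosols". For the amount, the input taken from the same study is "those with non-zero colony forming units (CFU) measuring bacterial load had a median of 2.5 CFU". The article assumes the same in controls and makes three power claims for the design stated as "by enrolling of 50 PWUD and 50 controls for Aim 3":

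- **Positivity:** "we have 80% power to detect a 70% positive CFU probability in PWUD".
- **Amount among positives:** "we have 80% power to detect a 2.5-fold increase in the median CFU value with Mann-Whitney test", with CFU assumed exponential.
- **Exhalation frequency:** "assuming exhalation pattern frequency of 23.9 in controls, we have 80% power to detect a 2-fold increase in median exhalation frequency".

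Other sections describe a different readout. Exhaled bioaerosol collection states "Droplet digital polymerase chain reaction (ddPCR) analysis will be used to detect", the target being Mtb in exhaled air. The same section modifies the cited chamber method by "reducing the sampling period to two consecutive 15-minute sessions and the removal of continuous", where the monitoring dropped is that of CO2, particles, temperature and humidity. Table 1 lists only a bioaerosol assessment by RASC for exhaled air. Assessment of primary objectives analyses the ddPCR data. It adds linear regression with drug use as main predictor, adjusted for bacterial load, HIV status, radiographic findings and other smoked substances, and uses GEE to account for matching on age and gender. Culture is described for sputum only.

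**The concern.** The Aim 3 hypothesis (Primary objectives) is that PWUD produce larger amounts of aerosolized Mtb after adjustment for bacterial burden. The outcome described for that comparison is a ddPCR result, a nucleic-acid measurement. A CFU count comes from culture, and exhalation frequency is another quantity again. Neither is described as recorded from the exhaled air, and neither appears in the analysis section. The tests behind the power claims (two proportions, Mann-Whitney) also differ from the adjusted regression with GEE.

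At stake is how an Aim 3 result is read. The article concludes that power is good for the hypothesized drug use effect. If the ddPCR comparison is null, a reader would judge it against a stated 80% that was worked out for another outcome and another test.

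**Working it through.** **Inputs.** From Sample size assumptions: control positivity 0.43, PWUD positivity 0.70, 50 per arm, control median 2.5 CFU among positives, 2.5-fold ratio, exponential distribution, and exhalation frequency 23.9 with a 2-fold ratio. No significance level is given for Aim 3, so two-sided 0.05 is assumed. The article gives no ddPCR positivity, copy number or SD.

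**Step 1: reproduce the positivity claim.** Pooled proportion = (0.43 + 0.70)/2 = 0.565.

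- SE under the null = sqrt(2 × 0.565 × 0.435/50) = 0.0992.
- SE under the alternative = sqrt((0.43 × 0.57 + 0.70 × 0.30)/50) = 0.0954.
- Power = Φ[(0.27 − 1.96 × 0.0992)/0.0954] = Φ(0.79) = 78.6%.

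Exact enumeration of the uncorrected chi-square test gives 80.0%, and Fisher's exact test 73.7%. The stated 80% reproduces.

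**Step 2: reproduce the amount claim.** Expected positives are 50 × 0.43 = 21.5 controls and 50 × 0.70 = 35 PWUD. Simulated Mann-Whitney power on exponential data with a 2.5-fold ratio (10,000 replicates):

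| Positives (control v PWUD) | Power |
|---|---|
| 21 v 35 | 79.6% |
| 22 v 35 | 80.5% |
| 21 v 21 | 69% |
| 22 v 22 | 71% |

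The stated 80% reproduces when PWUD positivity is already at the 70% alternative. If both arms are 43% positive, it is about 69%.

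**Step 3: the exhalation-frequency claim.** No dispersion is stated. If an exponential distribution is assumed here too, a 2-fold ratio with 50 v 50 gives about 83%, consistent with the claim.

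**Step 4: a ddPCR amount.** Take log10 copies, all 50 per arm quantifiable, and an unadjusted comparison of means. Then:

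- Power = Φ[log10(2.5)/(SD × sqrt(2/50)) − 1.96], with log10(2.5) = 0.398 and sqrt(2/50) = 0.2.
- Fold difference detectable at 80% power = 10^[SD × 0.2 × (1.96 + 0.84)].

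| Assumed SD (log10) | Power for 2.5-fold | Detectable fold at 80% |
|---|---|---|
| 0.5 | 98% | 1.9 |
| 0.75 | 76% | 2.6 |
| 1.0 | 51% | 3.6 |
| 1.5 | 26% | 6.9 |

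For example, at SD 1.0: 0.398/0.2 = 1.99, and Φ(1.99 − 1.96) = 51%.

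The SDs are assumptions; nothing in the article selects among them. The calculation also leaves out non-detects, covariate adjustment and matching, whose net effect on power cannot be signed from the article.

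**The case against.** The strongest reply is that this is a condensed article and the link may exist outside it. The reference that supplies the CFU figures (reference 38) is also cited for the ddPCR method, so it may hold usable ddPCR inputs. If control ddPCR positivity were near 43%, a two-proportion comparison would keep about 79% power. This stands, and it limits the point to power not shown to apply.

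Four stronger readings are tempting, and the article does not support them:

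- **CFU and exhalation frequency are not measured.** The article is silent and does not say so. Table 1 names the sampler without its readouts. Removing CO2 and particle monitoring proves nothing about exhalation frequency, because the article never says how it would be recorded.
- **Shorter sampling invalidates the 43% and 2.5 CFU.** The shortening is stated relative to reference 37, while those inputs come from reference 38, whose session length is not given.
- **High ddPCR positivity would leave no room for a difference.** That is true of a comparison of positive fractions: at an assumed 80% in controls, about 97.5% in PWUD would be needed for 80% power. The analysis section names no such comparison. For amount among positives the effect runs the other way: Mann-Whitney power for a 2.5-fold ratio rises to 93% with 40 v 40 positives and 97% with 50 v 50.
- **The among-positives claim is wrong.** It follows the 70% alternative in the preceding sentence and reproduces. Its dependence on that alternative is simply left for the reader to work out.

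None of this supplies a ddPCR basis for the 80%. Nor is it a detail left to a fuller document, since the article itself states the power and names a different readout and analysis.

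**Conclusion.** The point holds as a mismatch between the powered outcomes and the described outcome and analysis. There is no arithmetic error. The 80% is not shown to apply to the ddPCR amount under adjusted regression with GEE.

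Its size cannot be fixed from the article. Over the assumed log10 SDs, power for a 2.5-fold difference spans about 98% to 26%, so the true figure could lie on either side of 80%. A reader might infer that Aim 3 is underpowered, but the article does not establish that either. Confidence is high in the mismatch; the range is illustrative, resting on two-sided 0.05, fully quantifiable data and no adjustment.

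**What to change.** Rewrite the Aim 3 power paragraph:

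1. State power, or the detectable fold difference, for the ddPCR outcome under the planned comparison. Give the ddPCR positivity and variance inputs and their source, or a range if no source exists. Say how adjustment and matching are allowed for.
2. Either remove the CFU and exhalation-frequency claims, or state that these outcomes are measured and how they will be analysed.
3. If the amount-among-positives claim stays, say that its 80% assumes about 21 v 35 positives (43% v 70%) and falls to about 69% if both arms are 43% positive.

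The cost is one paragraph, plus measurement and analysis text if CFU or exhalation frequency is kept. Enrolment remains 50 v 50. The downside is that the stated power may become less favourable.

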### Assessment of primary objectives

For the primary analysis, TB prevalence among PWUD will be estimated according to the Volz-Heckathorn estimator [56]. Analysis will be performed using the RDS package within R (r-project.org) and sensitivity analysis will be implemented using the SS estimator. Prevalence of TB among PLHIV and those without HIV will be estimated and compared to community survey estimates [57].

For the second aim, we will estimate the prevalence of clustered cases via WGS in our population of PWUD and check additional thresholds to confirm robustness. A combination of software packages has previously been assembled with optimised parameters, together with in-house developed scripts, to create a customised pipeline for the analysis of mycobacterial genomes, with specific focus on variant calling. This customised pipeline has been automated for *Mtb* WGS data analysis [58]. An in-house developed script is used to identify the variants, and high confidence single nucleotide polymorphisms are then used in further analyses. Phylogenetic software will be used including RaxML, IQ-TREE and MEGA, and phylogenomic trees will be visualised using FigTree software [59–61]. For clustering analysis, the single nucleotide variants used for phylogenomic inference will be used to determine the variant distances between isolates and cluster analysis will be performed with the R-programming language, implementing the APE (Analyses of Phylogenetics and Evolution) and ADEGENET (Exploratory Analysis of Genetic and Genomic Data) packages.

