### Primary objectives

The Transmission Of Tuberculosis Among illicit drug use Linkages (TOTAL) study has three aims. The first is to assess the TB exposure, risk of disease progression, and disease burden among PWUD, including people living with and without HIV. We hypothesize that TB prevalence in PWUD will be significantly higher compared to results from a community-wide survey [32] and that the prevalence of incipient TB (host RNA signature presence) will be significantly higher among PWUD compared to the general community. We also hypothesize that PWUD living with HIV will have higher rates of incipient, subclinical, and clinical TB disease compared to those PWUD who are HIV negative.

Second, we aim to estimate the proportion of active TB cases that are the result of transmission within the social network of PWUD. We hypothesize that there will be a high proportion of linked isolates from Aim 1, reflecting predominance of recent transmission within this cohort. We also expect that persons with TB/HIV co-infection will more often appear as contacts with fewer links compared to persons with TB disease alone, reflecting their increased susceptibility to TB and their decreased ability to transmit TB.

Third, we aim to evaluate whether PWUD with TB disease have physiologic characteristics associated with more efficient TB transmission compared to people with TB disease who do not use drugs. Among individuals with TB, we hypothesize that PWUD will produce larger amounts of aerosolized *Mtb* than people who do not use drugs, after adjusting for bacterial burden (tested by mycobacterial culture time to positivity and GeneXpert Ultra). We will include people with and without HIV in each arm to assess any modifying effects of HIV, and record other smoked substances (tobacco, cannabis) and alcohol use to assess their impact as well.

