For Aim 3 Arm 1, 50 PWUD with active, untreated pulmonary TB will be recruited from Aim 2, and if necessary, the rest will be recruited from local health clinics. After providing informed consent, participants will receive a chest radiograph and undergo bioaerosol sampling. In Aim 3 Arm 2, study staff will recruit patients recently diagnosed with active TB disease who initiated treatment less than five days prior, or who are scheduled for treatment initiation from medical records at local health clinics, if they have provided permission to be contacted for this study. Study materials will also be placed within clinics and hospitals in the Worcester area so that individuals can contact study staff directly. Once individuals are screened for eligibility, informed consent is obtained and participants are enrolled, participants will then complete all study procedures that Arm 1 participants completed in Aim 2 and also undergo the Aim 3 procedures previously described.

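### Aim 2 targets cases caused by transmission within the drug-use network, but the stated estimator is the share of clustered PWUD isolates, which includes each cluster's first case and has no non-PWUD background

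*Protocol article*

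**What the plan says.** The Primary objectives section gives the target: "we aim to estimate the proportion of active TB cases that are the result of transmission within the social network of PWUD". The hypothesis in the same section expects that "there will be a high proportion of linked isolates from Aim 1, reflecting predominance of recent transmission within this cohort", so linkage is read directly as recent transmission within the group.

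For the analysis, the section on assessment of primary objectives says "we will estimate the prevalence of clustered cases via WGS in our population of PWUD and check additional thresholds to confirm robustness". The sample size section takes its input from other studies, in which "individuals who are in close contact with one another are linked by WGS in more than 70% of the sample", and states the precision for that proportion: "for a sample size of 50 individuals, our precision will be 24.6% meaning our 95% confidence interval (CI) will range from 56.2% to 80.9" per cent. The Methods section expects "projected 45–75 participants" in Aim 2.

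Three other elements bear on the point:

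- Methods and the recruitment section say that the Aim 2 estimate will rest on sequencing together with social links. Contacts and meeting places are collected by interview.
- A Bayesian classifier is described after the clustering paragraph. It is trained on links defined by sequencing plus social contacts, gives a probability for each pair, and allows for a source case that the study did not observe.
- For Aim 3 Arm 2 (50 people with TB who do not smoke illicit drugs), the recruitment section says that "participants will then complete all study procedures that Arm 1 participants completed in Aim 2". Table 1, row Aim 3b, lists culture, sequencing and a social contact survey. The stated analysis for Aim 3 concerns aerosol output. No stated analysis uses the Arm 2 sequences.

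**The concern.** The target and the stated estimator are different quantities, for two reasons.

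1. **Source cases.** A cluster of k sampled cases contains at most k − 1 cases infected, directly or through a chain, by another sampled member. The clustered share counts all k. As a measure of transmission observed among the sampled cases, it is therefore too high by at least the number of clusters divided by the number of cases.
2. **No background.** If only PWUD isolates enter the cluster analysis, two people infected separately by a strain common in the town cluster just as they would if one had infected the other. The Introduction itself warns that a high general burden may make transmission within this group hard to isolate.

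At stake is how the main Aim 2 percentage is read. A high clustered share would be taken as evidence that the drug-use network drives its own TB, which is the basis the article gives for later interventions. Part of that share may be index cases or general community transmission.

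**Working it through.** **Inputs from the protocol article**

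- Assumed linked proportion 70%, n = 50, interval 56.2% to 80.9%, full width 24.6% (Sample size assumptions).
- Projected Aim 2 cases 45 to 75 (Methods).
- Arm 2 size 50 (Methods).

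**Input not in the article:** the number of clusters c. It is assumed below and varied over its attainable range.

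**Step 1: reproduce the plan's interval.** Wilson score interval with x = 35, n = 50, z = 1.96, z² = 3.84:

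- centre = (0.70 + 3.84/100) / (1 + 3.84/50) = 0.7384/1.0768 = 0.686
- half-width = 1.96 × √(0.70 × 0.30/50 + 3.84/10,000) / 1.0768 = 0.123
- interval 56.25% to 80.90%, width 24.65%

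This matches the stated figures, so the arithmetic is right. It also confirms that the precision was computed for the linked share itself, with nothing deducted for source cases.

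**Step 2: remove one source case per cluster.** n-minus-one proportion = (clustered cases − c)/N. With 35 clustered of 50, a cluster needs at least two members, so c cannot exceed 17.

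| Assumed c | (35 − c)/50 | Wilson 95% interval | Shift from 70% |
|---|---|---|---|
| 1 | 68% | 54.2% to 79.2% | 2 points |
| 5 | 60% | 46.2% to 72.4% | 10 points |
| 7 | 56% | 42.3% to 68.8% | 14 points |
| 10 | 50% | 36.6% to 63.4% | 20 points |
| 17 | 36% | 24.1% to 49.9% | 34 points |

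These intervals treat cases as independent and c as fixed, so they are only a guide to scale.

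**Step 3: the ends of the projected case range.**

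- N = 45, 31 clustered: (31 − 1)/45 = 66.7% down to (31 − 15)/45 = 35.6%.
- N = 75, 52 clustered: (52 − 1)/75 = 68.0% down to (52 − 26)/75 = 34.7%.

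**Step 4: compare with the planned precision.** The lower arm of the plan's interval is 70 − 56.2 = 13.8 points. From seven clusters upward the shift is at least 7/50 = 14 points, so the choice of index can then move the answer by more than the sampling error the plan allows for. Trying other clustering thresholds changes which cases count as clustered. It does not remove the first case of each cluster.

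**Step 5: can the other Aim 2 elements close the gap?** The social links and the classifier bear on the background problem. The classifier gives probabilities for pairs, and its reference standard itself draws on sequencing links. The article states no rule that turns those probabilities, or the social links, into the proportion named in the objective. The only proportion with a stated estimator is the clustered share.

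**The case against.** The strongest reply has four parts.

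- **Aim 2 is more than one sentence.** A reader might infer that Aim 2 cannot tell network spread from community strains at all. The documents do not support that. Social links, contact interviews and a classifier that allows for an unobserved source are all planned. The limitation belongs to the clustered share taken alone. What remains is the missing step from those elements to the Aim 2 proportion. The full plan may contain that step, but the article does fix an estimator, and it is the clustered share.
- **The clustered share need not be too high for the aim.** A reader might infer that the headline is bound to overstate network transmission and that n-minus-one is the right figure. That does not follow either. The objective is not limited to transmission between sampled people. Recruitment stops at 750 in a hidden population, so a cluster's first case, or an unclustered case, may have been infected by an unsampled PWUD. Under incomplete sampling n-minus-one can be too low. This stands, and it is why both figures should be shown and neither alone should be the headline.
- **The size is assumed.** This also stands. With one large cluster the shift is only 2 points. No cluster count or size is in the article.
- **Arm 2 is a weak background, and silence is not exclusion.** The article does not say that Arm 2 isolates are left out of the tree, only that the estimate is made in PWUD. Fifty clinic patients are a thin sample of town strains. A mixed cluster may also be spillover from the network, which is part of the study's own premise. This limits what the Arm 2 isolates can show, but it is no reason to give sequences already planned no role.

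**Conclusion.** The point holds as a mismatch between target and estimator, and it is cheap to improve. The clustered share counts each cluster's first case as a result of transmission and, on its own, has no non-PWUD comparison. The planned social links and classifier address the second problem only in part, because nothing stated carries them into the reported proportion. At the plan's 70% of 50, removing one source per cluster gives between 36% and 68%. That range rests wholly on assumed cluster counts of 17 down to 1. The plan's own interval is computed correctly. The direction of error against the objective as worded is not established, since unsampled sources push one way while counted first cases and common town strains push the other.

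**What to change.** 1. Report two figures for Aim 2, described as lower and upper indices of observed recent transmission: the n-minus-one proportion (clustered cases minus number of clusters, over all sequenced Aim 2 cases) and the clustered share. Say that n-minus-one may be too low when PWUD sources are unsampled. Give the number and sizes of clusters.
2. Include the Arm 2 isolates in the same cluster analysis. Report the share of PWUD cases in PWUD-only clusters and the share in clusters that also contain Arm 2 cases.
3. Report the share of clustered PWUD cases that have a social link, so that the evidence for spread within the network is visible in the result.

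The cost is analysis time. No participants, samples or sequencing beyond those planned are needed. The drawback is that about 50 clinic-recruited Arm 2 isolates, fewer if some cannot be sequenced, will miss many mixed clusters, and a mixed cluster can itself arise by spillover from the network. The split should be presented as supportive evidence, not proof.
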